#### Additional measures

Additional questionnaires will be administered to obtain data related to: (1) sociodemographic information (age, sex, education level, employment status, income, religion and ethnicity); (2) pain history, including duration of pain, aggravating and relieving factors, other associated comorbidities; and (3) pain location using pain drawings. Other information such as resources required to conduct the trial (eg, cost) and time required to complete the recruitment of desired number of participants will also be recorded.^60^ Total duration of home exercises in each group will also be recorded.

Score on the credibility of treatment scale	Control condition is >0.50 SD credible than pain education group.	Develop a new control condition for the EP trial and pilot test to ensure that its credibility rating is <0.50 SD different from pain education group.	-	The credibility scores of the two conditions are within 0.50 SD units of each other.
Adherence to treatment	<50% attend the treatment session after randomisation.	Identify reasons for not attending the treatment session in order to increase attendance in the full trial.	50%–80% of the participants attend the treatment session.	80% or more of the participants attend the treatment sessions.
Difficulty scale	If ≥50% participants in the experimental group rate pain education as very difficult, very easy, easy or neither easy nor difficult.	Make the intervention a little more challenging if more than half of the participants report 1–3 out of 5 in the difficulty scale, by increasing the depth of the education, by adding more pain biology education content. Whereas if more than half participants report the intervention as very difficult, reduce the complexity. Re-evaluate complexity in a second cohort of at least five participants to ensure appropriate level of difficulty.	-	≥50% participants in the experimental group rate pain education as a ‘difficult’ intervention (4 out of 5 in the difficulty scale). This is the preferred difficulty level because we want pain education intervention to be difficult enough to challenge participants but not too easy or very difficult.

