*CD-RISC-10*, 10-item Connor-Davidson Resilience Scale; GROC, Global Rating of Change; PCS, Pain Catastrophizing Scale; *PROMIS*, Patient-Reported Outcome Measurement Information System; *T_1_*, enrolment time; *T_0_*, allocation time; *T_1_*, baseline assessment (before treatment); *T_2_*, during treatment; *T_3_*, 1 week post-treatment; *W*, assessment at the end of every week on Fridays.

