### Sample size

For a feasibility study, it is inappropriate to calculate sample size based on desired statistical power to detect a treatment effect,^35^ because the primary aim of the study is to assess if a full trial can or should be conducted. Feasibility outcomes are descriptive in nature; therefore, inferential statistics regarding treatment effects will not be computed. To achieve the primary objectives related to feasibility outcomes, the research team estimated that 40 participants would be adequate.^36^ Twenty patients will be randomly allocated to each treatment condition.

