7	Credibility and acceptability of the interventions	Treatment credibility will be assessed using five questions adapted from Borkovec and Nau.^63^ The questions will be modified to fit ‘Pain education’ and ‘Control group’ as a treatment for patients with LBP and will be administered to all the participants in both conditions. One, important cultural adaptation for the scoring will be made by changing the numerical scale proposed by Borkovec and Nau to a Verbal Rating Scale, because Numerical Rating Scales have been shown to be unsuitable in Nepalese with musculoskeletal pain, especially in those who are older and have low educational attainment.^64^ Responses for each of the five questions will be recorded on a Likert scale where, 0=‘*Not at all*’, 1=‘*A little bit*’, 2=‘*Somewhat*’, 3=‘*Quite a bit*’, 4=‘*Very much*’. The questions are: 1. How logical does the treatment provided seem to you for the management of low back pain? 2. How confident would you be that this treatment would be successful in reducing pain? 3. How confident would you be in recommending this treatment to a friend or family who also has LBP? 4. If you were having low back pain again, would you be willing to undergo such treatment? 5. How successful do you feel this treatment would be in reducing pain in other parts of the body, for example, knee pain? All the questions will be asked at baseline and at 1 week following treatment.	Mean of the total scores on the credibility scale will be computed separately for each condition. Between-condition differences in creditability will be evaluated using a t-test.
8	Adherence to the intervention	Adherence to treatment will be assessed by asking the participants in both conditions to maintain a record of daily home treatment that was followed by every participant. The participants will tick mark a box for every day for a total of 5 days between the two assessment time-points to indicate their adherence to prescribed home exercise programme. Additionally, participants will be requested to record any deviation of prescribed home treatment programme (eg, additional visit to the clinic and use of other interventions). Finally, question regarding non-adherence will be asked.	The total number of treatment adherence days will be summed for each treatment condition separately. Deviation from the treatment protocol will be recorded. Finally, the reasons for non-adherence will also be listed.

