### Data analysis plan

Descriptive statistics will be computed to describe the baseline and demographic characteristics of the study participants. As it is a feasibility study, level of significance and hypothesis testing regarding treatment efficacy will not be performed. Effect sizes representing between-group differences in change in the primary and secondary outcomes will be computed, but these effect sizes will not be considered as a criteria for sample size estimation for the full trial, nor as a criteria to proceed to the full trial, because of the inadequate power of the current feasibility study. Treatment effects for the secondary outcome measures will be presented as means, SD and CIs of the means. Difference between the mean scores of each secondary outcome will be compared with the minimum important change (MIC) values of the outcome measures, if the MIC scores are available. The analysis plans of the primary feasibility objectives are described in table 2.

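### The credibility row of Table 4 has a one-directional, incompletely worded trigger beside a symmetric proceed band, so one tail of the result has no decision

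*Protocol article*

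**What the plan says.** The section Criteria for feasibility states that the study will end in one of four decisions and refers to Table 4 for the criteria. The credibility row of that table contains:

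- Modify the protocol: "Control condition is >0.50 SD credible than pain education group".
- Action: build a different control condition and "pilot test to ensure that its credibility rating is <0.50 SD different from pain education group".
- Monitor closely: a dash.
- No close monitoring needed: "The credibility scores of the two conditions are within 0.50 SD units of each other".

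Table 2, item 7 (Outcome measures) defines the score as the total of five verbally rated questions. On timing it says: "All the questions will be asked at baseline and at 1 week following treatment". The key to Table 1 defines the first of these time points as "baseline assessment (before treatment", and the second is 1 week after treatment. The analysis is mean totals per condition, and "Between-condition differences in creditability will be evaluated using a t-test". On numbers, the Sample size section says: "Twenty patients will be randomly allocated to each treatment condition".

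**The concern.** A progression rule should assign a decision to every result that can occur. In this row the trigger has a direction, while the proceed band and the target of the corrective action do not. The part of the scale that is neither in the trigger nor in the proceed band is left with nothing, because the monitoring cell is blank. The trigger sentence also lacks its comparative, so the reader must guess which direction was intended.

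Credibility is one of the stated primary feasibility objectives. Patients and therapists cannot be blinded, and the secondary outcomes to be carried forward are largely patient-reported. A marked imbalance in credibility, in either direction, is therefore something the team would want to act on before a full trial. If the result falls in the unassigned tail, the decision will be made after the data are seen, and the rule is then no longer prespecified.

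A second gap adds to this. The score is taken twice, and the row says neither which reading decides nor which SD is the yardstick. The two readings could point to different cells.

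**Working it through.** The protocol gives no derived figure for this rule, so there is nothing to reproduce. The check is a partition of the scale, followed by the chance of landing in each part.

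**Inputs.** 20 per arm (Sample size); cut-off 0.50 SD (Table 4). The true credibility difference is not given and is assumed to range from 0 to 1.0 SD in favour of pain education. The drop-out levels of 15% and 30% are the band limits in the attrition row of Table 4: 20 × 0.85 = 17 and 20 × 0.70 = 14 per arm.

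**Partition.** Let d = (control mean − pain education mean) / SD.

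| Observed d | Trigger read as more credible | Trigger read as less credible | Trigger read as different |
|---|---|---|---|
| above +0.50 | modify | no cell | modify |
| −0.50 to +0.50 | proceed | proceed | proceed |
| below −0.50 | no cell | modify | modify |

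Either one-directional reading leaves one tail empty. Only the third reading closes the row, and the printed words do not say that.

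**Chance of the empty zone, natural reading.** With true difference δ and n per arm, SE(d) ≈ √(2/n) = √(2/20) = 0.316, and P(d < −0.50) = Φ((−0.50 − δ)/SE).

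- δ = 0: Φ(−0.50/0.316) = Φ(−1.58) = 0.057
- δ = −0.5: Φ(0) = 0.500
- δ = −0.8: Φ(0.30/0.316) = Φ(0.95) = 0.829
- δ = −1.0: Φ(0.50/0.316) = Φ(1.58) = 0.943

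Using the pooled sample SD, d/SE follows a noncentral t distribution with 2n − 2 degrees of freedom and noncentrality δ/SE:

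| n per arm | δ = 0 | δ = −0.5 | δ = −0.8 | δ = −1.0 |
|---|---|---|---|---|
| 20 | 0.061 | 0.504 | 0.827 | 0.941 |
| 17 (15% drop-out) | 0.077 | 0.505 | 0.808 | 0.926 |
| 14 (30% drop-out) | 0.099 | 0.505 | 0.786 | 0.906 |

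The value near 50% at δ = −0.5 is simply what follows when the truth sits on the cut-off. Under the reading less credible, the same figures apply to the other tail by symmetry.

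**After making the trigger two-sided (n = 20).** No value of d is without a decision. With δ = 0 the chance of triggering modification rises from 0.061 to 2 × 0.061 = 0.122 (normal approximation: 2 × 0.057 = 0.114). With δ = −0.8 it rises from about 0 to 0.827.

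**The case against.** The best reply has several parts, and some of it stands.

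*The direction depends on a missing word.* This stands. More credible is the natural way to complete the sentence, but the action, replacing the control, fits a control that is not credible enough at least as well. If different was meant, there is no gap in substance. This limits what can be said about which tail is empty. It does not rescue the row, because the printed text is incomplete and does not match its neighbouring cells.

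*The imbalance would still be seen.* This also stands. A much less credible control does not satisfy the proceed cell, and the means and t-test in Table 2 would show the difference. What is missing is an assigned decision, not detection.

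*Nothing about efficacy hangs on the row.* True: it is one of eight progression rows in a study that makes no efficacy claim. That bears on severity, not on whether the rule is complete.

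Three stronger readings are tempting and should not be adopted:

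- A reader might infer that the uncovered tail is the one case that would bias a full trial. A less credible control could favour pain education through expectation, but a more credible control would distort the comparison too, against pain education.
- A reader might infer that the row contradicts the Data analysis plan, where effect sizes are not to serve "nor as a criteria to proceed to the full trial". That sentence concerns between-group differences in change, whereas Table 4 compares credibility scores. No conflict is shown.
- A reader might infer that the pre-treatment reading is unusable and that the questionnaire must move to just after the session. Table 2 says the questions will be adapted to each condition, so the printed stem need not be the final baseline wording. Table 1 assigns this measure to the blinded assessor, so moving it would affect the assessor's role and the schedule. The documents do not require that change.

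**Conclusion.** The point holds as a defect in a stated decision rule. The trigger is incompletely worded and one-directional, the proceed band and the action's target are symmetric, and nothing else in the protocol assigns a decision to the remaining tail. On the natural reading with 20 per arm, a result falls there about 6% of the time by chance alone, and about 50%, 83% or 94% of the time if pain education is truly 0.5, 0.8 or 1.0 SD more credible. Those true differences are assumptions, and the figures also assume that the pooled SD is the yardstick. Losing 15% to 30% of participants changes them by only a few percentage points. The deciding time point and the SD are unspecified on any reading. This should be fixed before data are seen; it is not a fatal flaw.

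**What to change.** Reword the trigger cell so that it applies when the absolute standardised difference in mean total credibility score, using the pooled SD, is greater than 0.50 in either direction. The existing proceed cell and the action's target then fit it with little or no change. In the same row, name which of the two planned readings, baseline or 1 week, decides; the other can be reported descriptively.

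The cost is one table cell and one sentence, with no change to procedures, schedule or sample size. The statistical price is more false alarms: with equally credible arms and 20 per arm, the chance of being told to modify rises from about 6% to about 12%. The Data analysis plan needs no amendment on this account, and the questionnaire need not be moved.

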#### Dosage of the PEG intervention

A single approximately 1 hour pain education will be delivered to the PEG, because evidence indicates that: (1) interventions as brief as 5 min have been shown to have reassuring effects lasting for up to a year,^44^ and a single consultation has been found to be as reassuring as the multiple session interventions.^47^ We prefer a single session treatment over multiple session treatment, because for many patients in rural Nepal, it is difficult to deliver a multiple session treatment in reality. Thus, we plan to provide a single session delivering key concepts of Explain Pain, which will be reinforced by providing patient handouts to look at and read at home. In fact, a 1-hour session should be adequate to cover the key Explain Pain concepts by keeping the content simple and jargon free. Use of a plain language in the health-related education is important to adapt in low health literacy.^48^

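### Tables 2 and 4 use adherence for two different quantities: the home record that is collected has no decision criterion, and its summary as a sum per arm depends on how many records are returned

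*Protocol article*

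**What the plan says.** Intervention adherence is objective 7 in the protocol's Aims and objectives. Table 2, item 8 (Outcome measures) says how it is measured: participants in both arms "maintain a record of daily home treatment that was followed by every participant". In detail, "The participants will tick mark a box for every day for a total of 5 days between the two assessment time-points". Deviations and reasons for non-adherence are also collected. The analysis column states: "The total number of treatment adherence days will be summed for each treatment condition separately".

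Table 4 (Criteria for feasibility) has a row for adherence to treatment, with these bands:

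- Modify the protocol: "<50% attend the treatment session after randomisation".
- Proceed with close monitoring: "50%–80% of the participants attend the treatment session".
- Proceed without close monitoring: "80% or more of the participants attend the treatment sessions".

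The action attached to the row is "Identify reasons for not attending the treatment session in order to increase attendance in the full trial". Each arm has only one supervised session. For the experimental arm, "A single approximately 1 hour pain education will be delivered to the PEG", and the control session is set at one hour to match.

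**The concern.** The quantity that is measured does not decide, and the quantity that decides is not listed as the measure. Table 1 describes the intervention as one session plus a home programme through the week. Under Dosage of the PEG intervention, the protocol relies on handouts used at home to reinforce the single session, and both arms receive exercise instructions and reminders on five days. The home part is thus a substantial share of what is delivered, and it has no decision rule. A full trial could be declared ready on adherence when the home programme was hardly followed.

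The stated summary is a second problem. A sum of days per arm rises with the number of records returned, so a difference between arms may reflect follow-up and not adherence. Nor can a sum be read against bands expressed as percentages.

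**Working it through.** The plan gives no calculated figure to reproduce here; the sample of 40 is the team's estimate. The check compares the two tables and then applies the rule as written.

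**Inputs**

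- N = 40, 20 per arm (Sample size).
- 5 home days per participant (Table 2, item 8).
- Attendance bands: below 50%, 50%–80%, 80% or more (Table 4).

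**1. Which variable feeds which rule**

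| | Table 2, item 8 | Table 4, adherence row |
|---|---|---|
| Quantity | Home days ticked, 0 to 5 | Attended the session, yes or no |
| Summary | Days summed per arm | Percent of participants |
| Threshold | None | 50% and 80% |

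Table 1 places adherence at the one-week assessment (T3). That suits a home record; attendance would be seen at the treatment timepoint (T2). The other Table 4 rows cover blinding, recruitment, attrition, missing secondary outcomes, contamination, credibility and difficulty. None uses the home record. Total home-exercise duration, recorded under Additional measures, feeds no criterion either.

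**2. Table 4 applied to 40 participants**

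- 19 attend: 19/40 = 47.5%, modify.
- 20 to 31 attend: 50% to 77.5%, monitor closely.
- 32 attend: 32/40 = 80%, which falls in both upper bands as written.
- 33 to 40 attend: 82.5% to 100%, no close monitoring.

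**3. Does the home record change the result?**

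The maximum is 40 × 5 = 200 days. Suppose all 40 attend:

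| Home days completed | Percent of 200 | Adherence row |
|---|---|---|
| 0 | 0% | No close monitoring |
| 40 | 20% | No close monitoring |
| 100 | 50% | No close monitoring |
| 200 | 100% | No close monitoring |

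The classification is the same in every case.

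**4. The sum per arm (illustrative numbers)**

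Assume 20 records are returned in one arm and 15 in the other, each showing 4 days.

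- Sums: 20 × 4 = 80 and 15 × 4 = 60. The ratio is 60/80 = 0.75, an apparent deficit of 25%.
- Means: 80/20 = 4 and 60/15 = 4.
- Percent of prescribed days: 4/5 = 80% in both arms.

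If the five missing records were all drop-outs, total attrition would be 5/40 = 12.5%. That is under 15%, the best band of Table 4's attrition row, so that row would raise no warning.

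**The case against.** A reader might infer that poor home adherence can never affect the decision to proceed. The document does not support that. Criteria for feasibility says that the trial's results will inform the decision, and Limitation of the study says that the findings will inform recommended changes. Deviations, reasons for non-adherence and exercise duration are all recorded. Other primary objectives, such as willingness and satisfaction, also have no Table 4 row, so some outcomes appear meant to inform the decision descriptively. This stands, but only as informal judgement: the one row that carries the name adherence sets a formal rule, and that rule ignores the record.

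A reader might also infer that the attendance row is bound to pass because patients are already at the hospital. The protocol gives no attendance rate, does not describe inpatients and advertises on social media. It lists allocation, baseline and treatment as separate timepoints and promises no same-day session. Attendance after randomisation is a real feasibility question and deserves its own row.

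On the sum, the defence is that this is a one-line entry in a condensed article, that no rule or test uses it, and that a sum with a known n converts to a mean. This makes the point secondary. It does not remove it, because the article names the statistic and does not say that the number of records will accompany it.

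**Conclusion.** The mismatch is certain from the text. Adherence means home days in Table 2 and session attendance in Table 4, and no criterion in Table 4 uses the home record. Provided that at least 80% attend, the adherence row reaches its most favourable band for any home total from 0 to 200 days (subject to the overlap at exactly 80%). This concerns one row. It does not mean that the whole plan would return a favourable verdict, since seven other rows also count.

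The arm sum is a smaller, separate fault. Its size depends on how unevenly records are returned; the 25% figure rests on assumed returns of 20 and 15 and is not a forecast.

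The point should be corrected before the results are read, because a primary feasibility objective lacks a decision rule tied to its own measure.

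**What to change.** 1. In Table 4, label the existing row as session attendance, and say in Table 2 how attendance is recorded.
2. Add a separate home-adherence row based on the percent of the five prescribed home days completed. The investigators should choose and justify the cut-offs. The protocol gives no basis for a particular value on this scale. Reusing 50% and 80% is one option; applied to the mean percent with all 40 records returned, it would put fewer than 100 of 200 days in the lowest band, 100 to 159 in the middle and 160 or more in the highest.
3. State whether the cut-offs apply to the mean percent or to the proportion of participants reaching a given level. The choice matters: if all 40 complete 3 of 5 days, the mean is 60%, but the proportion completing at least 4 days is 0%.
4. In Table 2, item 8, replace the arm sum with mean days (SD) and percent of days completed among participants with a record, together with the number of records returned, by arm.

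The cost is wording in two tables and a justification of the cut-offs; the home record is already collected. The downside is that the adherence verdict may turn out less favourable.

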9	Satisfaction of treatment	All the participants in both the conditions will be asked to respond to the Patient Global Assessment of Treatment Satisfaction scale at 1 week following treatment.^65 66^ The question asked will be, ‘*How satisfied are you overall with the study treatment?*’ Responses to this question are made on a five-point categorical scale (0=‘*Very dissatisfied*’; 1=‘*Dissatisfied*’; 2=‘*Neutral or no preference’*; 3= ‘*Satisfied*’; 4=‘*Very satisfied*’).	Mean treatment satisfaction scores will be computed for each treatment condition separately. Between-condition differences will be evaluated using a t-test.
10	Difficulty in understanding the information provided by the physiotherapist.	All the participants will be asked about the difficulty in understanding the information provided by the physiotherapist. The question asked will be, ‘*How difficult was it for you to understand* the *information provided by the physiotherapist?*’ Responses will be provided on a 5-point Likert scale, where 1=‘*Very easy*’, 2=‘*Easy*’, 3=‘*Neither easy nor difficult*’, 4=‘*Difficult*’, 5=‘*Very difficult*’.	The differences in the difficulty in understanding the information provided will be compared between the two groups.
11	Difficulty in understanding the instructions for what to do.	All participants will be asked about the difficulty in understanding the instructions provided by the physiotherapist for what to do at home. The question asked will be, ‘*How difficult was it for you to understand the instructions provided by the physiotherapist for what to do at home?*’ using a on a 5-point Likert scale, where 1=‘Very easy’, 2=‘*Easy*’, 3=‘*Neither easy nor difficult*’, 4=‘*Difficult*’, 5=‘*Very difficult*’.	Frequencies and rates of each response category will be computed for each group separately.
12	Adverse events	All participants will be asked about any adverse events after treatment. All responses will be recorded verbatim.	The number of adverse events listed will be computed for each treatment condition separately. The responses will be analysed qualitatively (see text).

LBP, low back pain.

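### The 'Difficulty scale' row of Table 4 returns both 'modify' and 'proceed' at an exact half, and for some mixed ratings requires modification without defining an action

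*Protocol article*

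**What the plan says.** The section 'Criteria for feasibility' lists four possible decisions and says that one of them will be taken. Table 4 supplies the thresholds. Its 'Difficulty scale' row concerns the pain education group only, and its parts are:

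- **Modify trigger:** "If ≥50% participants in the experimental group rate pain education as very difficult, very easy, easy or neither easy nor difficult". This is every rating except 4.
- **Action, upward:** "Make the intervention a little more challenging if more than half of the participants report 1–3 out of 5 in the difficulty scale".
- **Action, downward:** "Whereas if more than half participants report the intervention as very difficult, reduce the complexity".
- **Monitor closely:** a dash, so there is no intermediate verdict.
- **Close monitoring not required:** "≥50% participants in the experimental group rate pain education as a ‘difficult’ intervention (4 out of 5 in the difficulty scale").

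Table 2 has two difficulty items, one on the information given and one on the home instructions. Both use a 5-point scale from 1 (very easy) to 5 (very difficult), so the arithmetic below is the same whichever item the row refers to. The denominator comes from 'Sample size': "Twenty patients will be randomly allocated to each treatment condition".

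**The concern.** A progression criterion should return one verdict for every possible result and, where it calls for a change, say which change. This row fails on both counts.

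- The two outer cells share an inclusive 50% bound on complementary sets, so an exact half satisfies both.
- The trigger is defined on a pooled share (too easy plus too hard), while the actions are defined on each share separately and with a stricter bound. The trigger can therefore fire when neither action applies.

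Difficulty in understanding is one of the stated primary feasibility objectives. In the affected results, the choice between modifying and proceeding, or between deepening and simplifying the content, would be settled after the ratings are known and not by the criterion.

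**Working it through.** **No stated figure to reproduce.** The protocol gives no calculation behind this row or behind the sample size; 'Sample size' says only that "the research team estimated that 40 participants would be adequate".

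**Notation.** Let E be the number of ratings 1–3, D the number of ratings 4 and V the number of ratings 5, with E + D + V = n = 20 (Sample size). Table 4 as written gives:

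- modify: E + V ≥ 10, which is the same as D ≤ 10
- proceed: D ≥ 10
- more challenging: E ≥ 11
- less complex: V ≥ 11

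**Step 1: count the splits.**

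- All splits (E, D, V): 22 × 21 / 2 = 231.
- Splits meeting 'modify': the sum of (21 − D) for D = 0 to 10 is 11 × 21 − 55 = 176.
- Splits with E ≥ 11: 1 + 2 + … + 10 = 55. By symmetry, 55 have V ≥ 11. All 110 also meet 'modify', because D is then at most 9.
- 'Modify' with no action defined: 176 − 110 = 66.
- Of these, D = 10 exactly (both verdicts): 11. 'Modify' only, with no action: 66 − 11 = 55.

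**Step 2: examples (E/D/V).**

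| Split | Modify? | Proceed? | Action defined? |
|---|---|---|---|
| 8/8/4 | yes, 12 of 20 | no | none: 8 and 4 are both below 11 |
| 10/5/5 | yes, 15 of 20 | no | none: 10 is not more than half |
| 6/10/4 | yes, 10 of 20 | yes, 10 of 20 | none |
| 11/5/4 | yes, 15 of 20 | no | more challenging |

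**Step 3: probability of the no-action gap.** Since E ≥ 11 and V ≥ 11 each imply D ≤ 9, and cannot both occur,

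P(gap) = P(D ≤ 9) − P(E ≥ 11) − P(V ≥ 11),

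with each term binomial on n = 20. The true shares are assumptions; the protocol gives none.

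| Assumed shares 1–3 / 4 / 5 (%) | P(D ≤ 9) | P(E ≥ 11) | P(V ≥ 11) | P(gap) |
|---|---|---|---|---|
| 40/40/20 | 0.755 | 0.128 | 0.001 | 0.627 |
| 50/40/10 | 0.755 | 0.412 | 0.000 | 0.343 |
| 60/30/10 | 0.952 | 0.755 | 0.000 | 0.197 |
| 70/25/5 | 0.986 | 0.952 | 0.000 | 0.034 |
| 80/15/5 | 0.9998 | 0.9974 | 0.000 | 0.002 |

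**Step 4: probability of the double verdict.** P(D = 10) = C(20,10) p¹⁰(1 − p)¹⁰, where p is the true share rating 4. This is 0.176 at p = 0.5, 0.117 at p = 0.4 or 0.6, and 0.031 at p = 0.3.

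**Step 5: other numbers of raters.** With 17 or 19 raters an exact half is impossible and the double verdict disappears. The no-action gap remains, in 36 of 171 and 45 of 210 splits. With 18 raters both defects occur: 10 ties and 45 further splits with no action.

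**The case against.** The best case for leaving the row alone is practical. The probabilities rest on shares the protocol does not state, and the no-action gap needs at least one rating of 5: if nobody chooses 5, fewer than ten ratings of 4 means at least eleven ratings of 1–3, and the upward action applies. The plan works to keep the content easy (plain language, image-heavy handouts, pretesting in 5–10 people), which makes a sizeable 'very difficult' share less likely. At 80/15/5 the gap is 0.2%. The double verdict is a single tie value and vanishes with an odd number of raters. No efficacy test hangs on this row, and informing later judgement is the purpose of a feasibility study.

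All of that stands as a limit on frequency and consequence. It does not make the cells consistent. The planned arm size is even, and the attrition and missing-data rows of Table 4 show that non-overlapping cells were intended elsewhere.

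A reader might infer more than the document supports, in three ways:

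- **That any mixed set of ratings leaves the direction open.** It does not: 11/5/4 is mixed and leads to a defined action.
- **That this is the only route by which the pain education may change.** The 'Pain education group' section separately provides for correction after pretesting and for modifications arising from the difficulty assessment.
- **That the re-check is itself defective** ("Re-evaluate complexity in a second cohort of at least five participants to ensure appropriate level of difficulty"). The article gives no pass mark and only a minimum size. A missing pass mark is detail that an article may leave to the full protocol, and any error rate for it would rest on an assumed cut-off.

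**Conclusion.** The point holds as an internal contradiction in a stated decision rule. Two facts follow from the text alone: at n = 20, 11 of 231 splits return both 'modify' and 'proceed', and a further 55 require modification with neither action applicable. These are counts of possible results, not probabilities.

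The probability is uncertain. Under assumed shares the gap runs from 63% (40/40/20) to 0.2% (80/15/5), and the 63% depends on a fifth of participants choosing 'very difficult'. It should not be read as the expected rate. The double verdict has probability 18% at most, when the true share rating 4 is one half, and needs an even number of raters.

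The consequence is an unresolved judgement before a later trial, not bias in a result of this one. No view is taken on which difficulty level is the right target or which way the content should change.

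**What to change.** Reword the one row:

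1. **Make the two verdicts exclusive.** For example, modify if fewer than 50% are in the target category and proceed if 50% or more are. At n = 20 this removes all 11 double verdicts and leaves 165 splits calling for modification.
2. **Reconcile the pooled trigger with the one-sided actions.** Step 1 alone leaves the 55 no-action splits untouched. Every result that calls for modification should map to one stated action, including results where the two off-target groups are equal (such as 6/8/6), which a simple larger-group rule would not resolve.

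The target level and the direction of change are for the investigators to set; the cells only need to agree with each other. The cost is the redrafting of one table row before the ratings are seen, with no added participants, visits or data.
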